### Economic analysis

#### Framework for the economic analysis

This trial evaluated a large number of alternative screening scenarios for identifying atrial fibrillation (2 screening strategies i.e. target v population; 6 screening methods i.e. pulse plus 3 types of ECG if pulse abnormal, and 3 types of ECG regardless of pulse; and 4 screening test interpretations, making 2*6*4 = 48 plus control and opportunistic screening = 50). The study has been powered to detect a difference in the targeted versus population arms, and in systematic screening versus routine clinical practice. However, the economic analysis will compare the cost-effectiveness of all alternative screening approaches using a modelling framework, whereby data will be drawn from the trial (where appropriate and available) and from external sources.

The use of a modelling approach allows the timescale for the economic analysis to be extended beyond the follow-up period allowed for in the trial. The use of such extrapolation will enable estimation of the incremental cost-effectiveness ratios (ICERs) for each approach:

Incremental cost per case detected

Incremental cost per life year gained

Incremental cost per quality-adjusted life year (QALY) gained

#### Data on consequences

The use of EQ-5D allows the measurement of broad aspects of quality of life. EQ-5D allows changes in health status to be measured but also valued, using the University of York Measurement & Valuation of Health general population survey tariff [27].

#### Cost data

The cost analysis adopted a broad perspective to include costs incurred within the health sector and by patients and carers. Data collection was undertaken on all trial patients in order to allow a stochastic cost analysis to be conducted. The focus of the data collection will be upon the key cost drivers which will include:

a) the resources required to establish screening (invitation to patient, follow ups, communication of results),

b) the time taken to carry out the various tests, and

c) the cost of the equipment (expressed as cost per test).

a), b) and c) will be based on data collected in the study.

The analysis adopted an incremental approach such that data collection concentrated on resource use differences between alternative screening scenarios. The process of collecting data on resource use was undertaken separately from data collection on unit costs. Resource use data on the screening process was principally collected within the trial. Unit costs were collected from published sources and a representative sample of NHS providers in order to increase generalisability. The methods used in collecting data will include patient questionnaires (see above) and review of patient records (both GP and hospital). Data on private costs were collected from a survey of a sub-cohort of the trial population.

#### Cost effectiveness analysis

The plan for the analysis is:

1. Report a cost consequence analysis, which will involve providing a full description of all important results relating to costs and consequences.

2. Conduct both a cost-effectiveness analysis and a cost utility analysis (using data on true positive cases detected as the measure of effect and data on EQ-5D to estimate QALYs).

An incremental approach will be used in order to compare the large number of alternative screening strategies.

We are interested in comparing the mean costs per patient since our concern is with predicting overall programme costs. However, the data on costs are likely to have a skewed distribution. Therefore, the plan for the analysis of costs is:

1. To explore the nature of the distribution of costs

2. If required, to use non-parametric comparison of means (e.g. bootstrapping)

3. If the distribution of the data is approximately normal, parametric methods will be used.

This approach is in line with recent recommendations [26].

If missing data are a problem at the economic analysis stage, then imputation techniques will be employed.

Longer term costs and consequences will be explored by extrapolating beyond the end of the trial using a modelling framework using data from a range of trial and non-trial sources. The precise form of modelling is yet to be determined, but is likely to be either Markov or Discrete Event Simulation, depending upon the extent to which the Markov assumptions are justified. An advantage of using such an approach is that it will allow the additional costs of increasing survival to be explicitly incorporated into the analysis. In particular, modelling will provide estimates of the optimal frequency of screening for AF, based on the estimates of incidence and prevalence from the trial.

Identifying untreated patients with AF will have implications for service provision. These will depend upon the prevalence of atrial fibrillation, the screening mechanism employed, the use made of echocardiography, and the additional requirements for anticoagulation monitoring. The separate parallel study, BAFTA, will provide empirical data that will allow such implications for service provision to be assessed. The modelling exercise, which will draw on both SAFE and later BAFTA results, will combine best estimates of both screening and anticoagulation options.

The robustness of the results of the economic analysis will be explored using sensitivity analysis [27]. This will explore uncertainties in the trial based data itself, the methods employed to analyse the data and the generalisability of the results to other settings. Uncertainty in the confidence to be placed on the results of the economic analysis will be explored by estimating cost-effectiveness acceptability curves. These plot the probability that the intervention is cost-effective against threshold values for cost-effectiveness.

### Inclusion and exclusion criteria

#### Inclusion criteria

Patients aged 65 years or over (65+).

#### Exclusion criteria

Patients who were terminally ill.

#### Randomisation

Randomisation of practices and patients was performed by statisticians from the Department of Primary Care and General Practice at The University of Birmingham. Cluster randomisation of practices to intervention or control was stratified by Townsend quartiles and practice size. Computer searches were carried out to identify cases of known AF, within the sample of patients identified above, using a published strategy [15]. The randomisation of patients within the intervention practices ensured that the study patients in each practice were divided equally between systematic and opportunistic screening arms and also that there was an even distribution of patients with known AF between the two arms. Patients within the systematic screening arm were identified by computerised record searching as either being at high risk (target population) or moderate risk (non-target population) of AF by recognised criteria [28,11].

#### Cleaning of lists post randomisation

Following initial sampling of the total population the list of patients from each practice were returned to the practices who were asked to remove any patients who had died, moved or were terminally ill. Patients removed following this process were replaced with patients from a reserve list, which had been randomised at the same time as those on the initial lists.

#### Patient information and consent

Patients aged 65+ who were selected to the systematic screening arm received an information sheet with an invitation letter to attend the ECG clinic. Entry to the trial was discussed with the practice nurse at the clinic. The practice nurse then obtained written consent from those patients who were willing to participate.

Study patients found opportunistically to have an irregular pulse were given an information sheet and invited to attend the screening clinic.

#### Practice staff education and ECG training

GPs and other members of the primary health care team in the intervention practices attended investigator days at which they were given educational materials informing them of the importance of detection of AF, and the treatment options that are available. The materials encouraged them to consider opportunistic screening of patients.

Members of the primary health care team in control practices received no educational input from the research staff.

Practice nurses attended an ECG training day prior to starting the ECG screening clinics. Training included how to perform an ECG (using the Biolog) to ensure a standardised high quality tracing and basic ECG interpretation (specifically how to identify AF).

### Computerised and note searches of GP records

#### Prevalence and incidence data

Computer searches were carried out to identify cases of probable AF in the 15,000 study patients using a published strategy [15]. Searches were tailored towards the information that is held on computer in each practice. If practices hold AF registers, or use READ diagnosis coding, then these were used. In addition, a search was carried out to identify prescriptions of digoxin, a beta-blocker, a class 1,3 or 4 anti-arrhythmic agent, aspirin or warfarin. This information was recorded into computerised case report forms.

Case notes of patients identified as 'known' or 'probable' AF in any of these computer searches were reviewed for mention of a diagnosis of AF. AF diagnosis were drawn from hospital letters stating the existence of the condition or ECG recordings from the last 5 years.

An additional 5% random sample of case notes of patients not identified as 'known' or 'probable' AF by computer searching were reviewed (750 in all) to estimate how many other patients who are known to have AF were not identified by the computer searches. If this had revealed a significant number of extra cases of known AF, then the sample size for manual searching would have been increased to allow a precise estimate of the baseline rate of known AF. Unidentified extra AF cases were not found to be significant so no additional note search was required.

The same computer searches on both intervention and control practice patients notes were performed prior to, and 12 months after, commencement of screening.

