### The appropriate screening strategy to be employed

#### Opportunistic screening

The simplest strategy was *opportunistic case finding*, where a health care professional took the opportunity to feel a patient's pulse during a consultation. If the pulse is irregular, they might make a clinical diagnosis of AF, or request/perform an electrocardiogram (ECG) as a confirmatory test. However, opportunistic case finding is likely to miss a significant proportion of people who would otherwise have benefited from treatment. For example, detection of hypertension in general practice was traditionally detected in an opportunistic way until the introduction of health checks with the 1990 GP contract. The Health Survey for England shows that in 1991, 42% of the population over the age of 75 had hypertension for which they were not taking any medication [10]. This figure had fallen to 31% by 1994, after the GP contract had taken effect.

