### Statistical analysis

Intention to treat analysis will be used.

Any previously known Atrial Fibrillation cases will be subtracted from the totals obtained at the end of the study to ensure there is no double counting in the incidence figures.

Chi-squared, independent t-tests and log-linear models will be used to describe demographic data. If there are differences between the groups this may need to be adjusted for in later analyses.

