#### Screening clinics

All patients in the systematic screening arm and those found to have an irregular pulse in the opportunistic screening arm of the study were invited to attend an ECG screening clinic. At the clinic the practice nurse explained the aims of the study and answered any questions about the study. Written informed consent to participation in the study was obtained from the patient. The nurse then recorded baseline information on age, sex, present smoking and alcohol status and past medical history, including previous diagnosis of AF, and any treatment the patient may be receiving for AF. Radial pulse rate, and whether regular or irregular, was noted. A 12 lead ECG, the gold standard by which other traces were compared, was then recorded using the Biolog machine, which was also able to produce a trace corresponding to the single lead thoracic placement and a rhythm strip of lead II. Finally, the patient was asked to complete an acceptability questionnaire.

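### The proof rule for baseline AF is narrower than AF the practice already knows about, so some known AF can be counted as newly detected, mainly in the systematic arm

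*Protocol article*

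**What the plan says.** Three parts of the protocol article bear on who counts as already having AF.

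- **Record search** (Prevalence and incidence data). The search draws on registers, codes and prescriptions: "If practices hold AF registers, or use READ diagnosis coding, then these were used". Then, "Case notes of patients identified as 'known' or 'probable' AF in any of these computer searches were reviewed for mention of a diagnosis of AF". The evidence accepted is described in one sentence: "AF diagnosis were drawn from hospital letters stating the existence of the condition or ECG recordings from the last 5 years". The search is repeated later: "The same computer searches on both intervention and control practice patients notes were performed prior to, and 12 months after, commencement of screening".
- **Power assumptions** (Sample size and power calculations). The baseline quantity, A1, is AF that the practice already knows about, taken as 3%. The change in control practices is expected to be about 0%.
- **Subtraction** (Statistical analysis). "Any previously known Atrial Fibrillation cases will be subtracted from the totals obtained at the end of the study". No source is named for deciding what was previously known.

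Two further points matter. In the systematic arm, patients with a history of AF are invited to the clinic like everyone else (Methods, below Figure 1). At the clinic the nurse records "past medical history, including previous diagnosis of AF, and any treatment the patient may be receiving for AF", but the article does not link this field to the subtraction.

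**The concern.** The article accepts that a professional who feels an irregular pulse may act without an ECG: "they might make a clinical diagnosis of AF". AF of that kind, or AF shown only on an ECG more than 5 years old, can be well known to the practice and yet lack the evidence that the record search accepts.

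Randomisation should spread such patients evenly across the arms. What differs is the chance of acquiring qualifying proof during the study. A systematic-arm attender receives a 12-lead ECG whatever the history. An opportunistic-arm patient receives one only after an irregular pulse. A control patient receives none from the study. Old AF re-found on a study ECG would therefore raise the detection rate more in the screening arms than in control practices. It would also lower the apparent incremental cost per case, the other primary outcome.

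The Background section itself reports that, in an earlier four-practice UK study, most of the cases found by systematic screening had already been diagnosed.

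**Working it through.** **The plan's own figure.** Comparisons (a) and (b) need 1,236 patients per arm to detect 0% against 1% with 90% power at the 5% level. For two proportions, two-sided, with δ = 0.01 and mean proportion 0.005:

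- n = [1.960 × √(2 × 0.005 × 0.995) + 1.282 × √(0.01 × 0.99)]² / 0.01² = 1,044 after rounding up.
- The continuity correction, (n/4) × [1 + √(1 + 4/(nδ))]², gives 1,236. This matches the article.
- The design factor is 1 + 199 × 0.015 = 3.985, and 1,236 × 3.985 = 4,925, which the article rounds to 5,000.

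A 1-point difference is thus the effect these practice-level comparisons were built to detect. The article also names 1 point as the minimum worthwhile change, for targeted screening against routine practice.

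**Inputs for the possible bias.**

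- Known AF at baseline: 3% (Sample size and power calculations).
- Screening uptake: 66% (same section, comparison f).
- u, the share of known AF with no qualifying letter or ECG: not given in the article. Assumed range 5% to 30%.

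**Worst case, systematic arm.** False yield = 3% × u × 66%:

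| u | False yield (points) | Patients per 5,000 |
|---|---|---|
| 5% | 0.10 | 5 |
| 10% | 0.20 | 10 |
| 20% | 0.40 | 20 |
| 30% | 0.59 | 30 |

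To create the whole 1-point difference, u would have to be 1 / (3 × 0.66) = 51%.

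**Sensitivity to the known share.** The article cites estimates from 30% to 76% of AF being known. With its 6% prevalence, known AF is 1.8% to 4.56%. At u = 10% the false yield is then 1.8% × 10% × 66% = 0.12 points to 4.56% × 10% × 66% = 0.30 points.

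**Offset in control practices.** Suppose, as an illustration, that 25% of such control patients gain a letter or routine ECG by 12 months. At u = 10% the control arm gains 3% × 10% × 25% = 0.075 points, and the excess in the systematic arm falls from 0.198 to 0.123. If the 34% of systematic-arm patients who do not attend gain proof at the same rate, 3% × 10% × 34% × 25% = 0.026 points return and the excess is about 0.15.

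**Does the notes sample settle it?** The article reports of its 750-note check that "Unidentified extra AF cases were not found to be significant so no additional note search was required". That sample was drawn from patients whom the computer search had not flagged. The patients at issue here are those whom a register, code or prescription did flag, but whose notes hold no qualifying letter or ECG. The check does not test them.

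**The case against.** The strongest reply is that no sentence in the article says GP-coded AF is to be treated as not known. The searches use registers and diagnosis codes, the notes are read for any mention of AF, and the subtraction covers any previously known case. The clinic also collects prior diagnosis and treatment, so the data to remove re-found cases exist. Requiring documentary proof is a defensible choice where the 12-lead ECG is the gold standard. All of this stands, and it limits the point to an evidence rule that is narrower than the stated baseline and a subtraction that does not say which of the two governs.

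A reader might infer more than this. The documents do not support four stronger readings:

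- **That the misclassification occurs in the screening arms only.** The same search runs in control practices at 12 months, so a new letter or routine ECG there also turns an unproven case into a new one. The opportunistic arm reaches a study ECG only after an irregular pulse. The effect is differential, not exclusive.
- **That any proof older than 5 years fails.** The limit may attach to the ECGs alone. An old hospital letter would then qualify, which could cover much long-standing AF.
- **That the plan directs these cases to be counted as new.** This follows only if the evidence sentence governs the subtraction.
- **That the 750-note check yields a bound on this bias.** The article reports no count from the check, and it concerns unflagged patients.

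The objection that the source of the subtraction is mere operational detail does not dispose of the point, because the evidence rule is stated and differs from the stated baseline.

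**Conclusion.** The concern holds in a limited form. As written, the evidence rule can leave AF that the practice already knows about outside the baseline count, and neither the subtraction rule nor the notes sample closes that gap. Any resulting error favours screening, most of all in the systematic versus control comparison.

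Its size cannot be determined from the article. The range of about 0.1 to 0.6 points, which is 10% to 60% of the minimum worthwhile difference, rests wholly on the assumed 5% to 30% of known AF without qualifying proof. At the article's 3% and 66% it is a worst case: every such attender is in AF at the clinic, no control patient is newly documented, and the clinic history is not used. Paroxysmal AF in sinus rhythm at the clinic would not be re-found, and use of the clinic history would take the bias towards zero. This is a possible material bias in a primary outcome. It is not evidence that a 1-point difference would be spurious.

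**What to change.** 1. For the subtraction, define previously known AF as any AF diagnosis recorded in the notes before screening started: a GP entry or code, a hospital letter, or an ECG of any date.
2. Check the pre-screening notes of every apparent new case against that definition, in all three arms.
3. Use the AF history recorded at the clinic as a consistency check, not as the sole ground for exclusion. Control patients have no such field, so removing cases on it alone would create a new asymmetry.
4. State whether the 5-year limit covers hospital letters as well as ECGs, and report the result under the proof rule as a sensitivity analysis.

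The cost is low: a changed definition, plus a notes check limited to apparent new cases, using records and a clinic field that the study already has. The downside is a slightly lower yield, with some unproven GP diagnoses counted as known; the sensitivity analysis shows how much this matters.

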#### Screening clinics

All patients in the systematic screening arm and those found to have an irregular pulse in the opportunistic screening arm of the study were invited to attend an ECG screening clinic. At the clinic the practice nurse explained the aims of the study and answered any questions about the study. Written informed consent to participation in the study was obtained from the patient. The nurse then recorded baseline information on age, sex, present smoking and alcohol status and past medical history, including previous diagnosis of AF, and any treatment the patient may be receiving for AF. Radial pulse rate, and whether regular or irregular, was noted. A 12 lead ECG, the gold standard by which other traces were compared, was then recorded using the Biolog machine, which was also able to produce a trace corresponding to the single lead thoracic placement and a rhythm strip of lead II. Finally, the patient was asked to complete an acceptability questionnaire.

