#### The most appropriate screening test for AF

12-lead ECG is recognised as the gold standard test, but this test is time consuming (taking at least 15 minutes to perform in an outpatient setting). Therefore, it is important to consider simpler tests. This study assessed simpler methods compared to the gold standard, both in terms of accuracy, time taken and patient acceptability. These include taking the pulse, and simpler ECGs.

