#### Secondary objectives

• To evaluate the relative cost-effectiveness of screening methods for AF diagnosis, comparing 12 lead ECG (gold standard) with pulse taking, lead II rhythm strip from standard ECG limb leads alone and single lead thoracic placement ECG.

• To evaluate the most cost-effective method of test interpretation, comparing cardiologist (gold standard), with GP, practice nurse, or computerised diagnostic software.

• To assess the differing combinations of screening strategies and procedures in terms of patient acceptability and impact on patient quality of life, including any psychological effects of screening.

• To determine the community prevalence of AF in people 65+.

• To evaluate the value of clinical assessment and echocardiography as additional methods of risk stratification for thromboembolic disease in patients with AF.

• To evaluate the service provision implications should screening for AF become a national programme, and identify the optimum screening algorithm for identification of patients with AF.

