#### Secondary outcomes

• Cost effectiveness of 4 different methods of screening for AF. The cost data focused on the difference in the cost of the equipment and the time taken for each of the different methods of screening to be completed. This was from both an NHS and patient perspective.

• Cost effectiveness of 4 different methods of ECG interpretation. The cost data focused on the difference in the cost of the grade of staff interpreting the ECG and the accuracy of their interpretation.

• Overall community prevalence and incidence of AF

• Patient acceptability to AF screening was measured using an adapted version of the screening specific questionnaire used in the Colorectal Screening Programme [18]. Patient uptake of screening was also monitored. The impact on quality of life was assessed using EQ-5D [24,25]. Patient anxiety was measured using the Spielberger 6 item Anxiety Questionnaire [17].

• Modelling techniques were used to identify the implications of AF screening on health service provision nationally. This included the effect on echocardiography and anti-coagulation clinic provision.

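### Simpler ECGs are print-outs of one 12-lead recording, so the trial cannot compare acceptability between ECG types or observe time and equipment cost for a stand-alone thoracic ECG

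*Protocol article*

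**What the plan says.** In *The most appropriate screening test for AF* (Background), the protocol article states: "This study assessed simpler methods compared to the gold standard, both in terms of accuracy, time taken and patient acceptability". It goes on: "These include taking the pulse, and simpler ECGs". The reason given there for wanting a simpler test is the length of a 12-lead ECG, put at 15 minutes or more in outpatients.

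*Secondary objectives* has two relevant items. One is the relative cost-effectiveness of the tests, "comparing 12 lead ECG (gold standard) with pulse taking, lead II rhythm strip from standard ECG limb leads alone and single lead thoracic placement ECG". The other is "To assess the differing combinations of screening strategies and procedures in terms of patient acceptability and impact on patient quality of life". *Secondary outcomes* costs the four methods from equipment and the "time taken for each of the different methods of screening to be completed". *Cost data* lists set-up resources (a), test time (b) and equipment cost per test (c), and then says "a), b) and c) will be based on data collected in the study".

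The procedure itself is in *Methods* and *Screening clinics*. A clinic attender has a radial pulse check and a 12-lead ECG on one machine, "which was also able to produce a trace corresponding to the single lead thoracic placement and a rhythm strip of lead II", and then fills in one acceptability questionnaire. *Methods* calls the two simpler traces print-outs. For the later reading exercise it allocates each recorded ECG at random to one of three print formats.

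**The concern.** Printing one recording in several formats is a sound way to compare how accurately each format is read. It gives no information on what it is like to undergo a simpler ECG, or how long one takes, because nobody undergoes one. The article nevertheless names time and acceptability among the quantities compared, and gives the study as the source of per-test time and equipment cost.

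Two things are at stake. A statement about the acceptability of the lead II or thoracic ECG relative to the 12-lead would have no data behind it. And the main argument for a simpler ECG, that it saves time, would rest on inputs labelled as trial data that the described procedure does not generate.

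**Working it through.** No sample size or error rate is in dispute. The check sets what is to be compared against what the described procedure can supply.

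1. **ECG type is a print format.** *Screening clinics* could be read as saying only that the machine is capable of the simpler traces. *Methods* settles it: the traces are print-outs, and all recorded ECGs were printed in one of three formats for readers. No section describes a patient who has only a limb-lead or thoracic recording.

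2. **Acceptability is measured once per visit.** *Methods* and *Screening clinics* both place the questionnaire after screening. It follows the pulse check and the full 12-lead ECG.

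3. **What each ECG type can supply under this procedure:**

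| Quantity | 12-lead | Lead II strip | Single-lead thoracic |
|---|---|---|---|
| Accuracy and interpretation | yes | yes, from print-out | yes, from print-out |
| Time as a test on its own | can be timed | only from step times, not described | no |
| Equipment cost as a test on its own | study machine | no separate device described | no separate device described |
| Acceptability | within the rating of the whole visit | no | no |

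The pulse check is a separate step and could be timed, so the point is confined to the ECG types.

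4. **Reach in the economic analysis.** *Framework for the economic analysis* counts 2 strategies × 6 methods × 4 interpretations = 48, plus control and opportunistic screening = 50. This reproduces. The 6 methods are three ECG types used after an abnormal pulse and the same three used regardless of pulse. Two of the three types are simpler ECGs, so 2 × 2 = 4 of the 6 methods use one. That gives 2 × 4 × 4 = 32 of the 48 systematic scenarios needing a time and an equipment cost for a simpler ECG. Half of these, 2 × 2 × 4 = 16, need them for the thoracic ECG.

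5. **Consequence for cost.** If the whole-visit time or the study machine's cost were entered for every ECG type, the difference in time and equipment between types would be zero by construction and any saving from a simpler ECG would be hidden. The article does not say that this will be done.

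**The case against.** The strongest reply is that a condensed article is being faulted for silence.

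- **Acceptability.** *Secondary outcomes* defines acceptability for AF screening as such, and part (a) of the secondary objectives under *Statistical analysis* analyses it by screening strategy. No analysis by ECG type is planned. This stands, and it confines the acceptability problem to the Background claim and to the word procedures in *Secondary objectives*. It does not rescue those two statements, which no analysis of a single whole-visit rating could support.
- **Time.** Step timing within the visit, or a separate timing exercise, may be in a full protocol that is not shown. This stands for lead II, whose time can be built from the limb-electrode and recording steps. It does not carry over to a thoracic ECG that is never performed on its own.
- **Cost inputs.** *Framework for the economic analysis* allows external data, *Cost data* takes unit costs from published sources and NHS providers, and *Cost effectiveness analysis* plans sensitivity analysis. This stands: the model has a legitimate route to these inputs. But that route does not fit the statement in *Cost data* that items b and c rest on study data, so that statement needs correcting.

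A reader might infer that simpler-ECG time is never observed at all, that the 12-lead ECG is bound to dominate, or that the error can be put in nurse-hours. For example, take 66% of 5,000 = 3,300 attenders and 15 minutes for a 12-lead ECG. Assumed times of 2, 5 or 8 minutes for a simpler ECG then give 3,300 × (15 − t)/60 = 715, 550 or 385 hours. The documents do not support these readings. Lead II step times are not excluded, no section assigns the 12-lead time to the simpler ECGs, the 15 minutes is an outpatient figure and not a practice-clinic one, and the shorter times are assumptions.

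**Conclusion.** The point holds in a limited form. As the procedure is described, acceptability cannot be compared between ECG types, and time and equipment cost for a stand-alone thoracic ECG cannot be trial observations. Lead II time can be one only if component steps were timed.

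In extent, this touches two of the four screening tests and 32 of the 48 systematic scenarios. Its numerical effect on cost-effectiveness is unknown and cannot be derived from the article. The conclusion rests on reading the simpler traces as print-outs of the 12-lead recording, which *Methods* supports, and on the questionnaire rating the visit as a whole. Comparisons of accuracy and interpretation between formats are not affected, nor is the primary comparison of AF detection between strategies.

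**What to change.** 1. Limit conclusions on acceptability to the screening visit or strategy. Remove acceptability from the between-test claim in *The most appropriate screening test for AF*, and state in *Secondary objectives* that procedures does not extend to ECG types.
2. Amend *Cost data* so that time and equipment cost for the simpler ECGs are external model inputs with a stated source. If step times were logged in the clinics, say so and derive the time inputs they can support, such as lead II, from them.
3. Vary these inputs over a stated range in the sensitivity analysis already planned under *Cost effectiveness analysis*.

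The cost is wording and some modelling work. *Discussion* says a draft report has already been submitted, so adding time fields to the clinic form is no longer an option. The price is a narrower acceptability claim and wider uncertainty for the scenarios that use a simpler ECG.
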